### Randomization

A randomization schedule was created with a web-based, computerized random number generator. We maintain allocation concealment and eliminate possible selection or recruitment biases by keeping the randomization schedule concealed from on-site staff engaged in recruiting. A randomization schedule was generated by the PI who does not have any contact with participants, and a sealed envelope with the sequentially numbered randomization schedule was prepared prior to recruitment of any participants. After a project coordinator determines eligibility for a prospective dyad and obtains informed consent, the PI is notified and then opens the sealed envelope. The group assignment based on the predetermined sequence for that participant to 1 of the 2 groups is revealed at that point. If the participant is in the TAP group, an interventionist is then assigned to that participant. In order to control bias and preconceptions in collecting data, the interventionist does not collect baseline or follow-up data from participants with whom they intervene.

### Intervention Implementation

The TAP is carried out by a psychology PhD student interventionist who underwent rigorous training. The interventionist is responsible for scheduling and following up with caregivers under his or her care, and the same interventionist administers all sessions for a single caregiver in order to maintain consistency across sessions, unless extenuating circumstances arise. To ensure TAP intervention fidelity, the PI reviews the interventionists’ recordings for the first full 5 sessions that the interventionist conducts. A checklist was developed that covers the content specific to each session and an assessment of the interventionist’s interaction with the caregiver. The PI provides a summary of strengths, shortcomings, and recommendations for improvement so that any errors can be corrected immediately and not be repeated.

### Intervention

#### Session 1

The PI and collaborators trained a psychology PhD student to serve as an interventionist and provide the TAP. In preparation for Session 1 with the caregiver, the interventionist delivering the TAP meets with the facility’s rehabilitation team (and in particular, the SCI interdisciplinary team collaborators and consultants on the grant) to identify the primary difficulties anticipated for the individual with SCI after discharge. The interventionist takes notes on the particular needs and bring these notes to Session 1 with the caregiver. Before discharge, the interventionist implements Session 1, a 1-hour meeting with each caregiver in the intervention group only. The primary focus of Session 1 is to orient the caregiver to the TAP and prepare the caregiver for discharge home. The interventionist provides the caregiver the guidebook and orientation to it, encouraging the caregiver to use it as a resource (caregivers in the control group receive a copy of the caregiving guidebook after the final data collection). The interventionist asks what concerns the caregiver has caring for the individual with SCI after discharge, taking notes on the caregiver’s responses. The interventionist shares with the caregiver the difficulties that the rehabilitation team had anticipated the individual with SCI will experience after discharge. The interventionist provides support and helps the caregiver problem solve caregiving related to these issues.

#### Sessions 2-5

The interventionist administers four 1-hour telehealth clinic-to-home sessions with the SCI caregiver at 1, 2, 4, and 6 weeks after hospital discharge. One of the rehabilitation centers already had in place secure and encrypted telehealth technology that allows an interventionist on-site to meet virtually with a caregiver at home via personal computers or mobile devices. For caregivers who do not have a personal computer, mobile device, or adequate internet connection, a telephone-based approach is used. The individual with SCI may or may not be in the same room as the caregiver during these sessions, depending on the wishes of the caregiver. These sessions involve the same general format. The interventionist brings his or her notes from the previous sessions and from the rehabilitation team’s input. The interventionist reviews the content of these notes with the caregiver, checking in to see whether the problems are still present and to what extent. The interventionist engages in supportive problem solving and refers the caregiver to the guidebook sections relevant to the issues, walking the caregiver through those sections. Because of this format, the TAP is specifically designed for interventionists to tailor its use in future studies or administrations not only according to possible facility differences in what may be necessary for the intervention but also for differences in caregiver responsibilities and needs within a single facility. The entire structure of the TAP is centered around the caregiver’s most pressing needs. The interventionist takes notes on the continued problems and strategies for resolving them.

### Data Collection

#### Data Collection 1

After enrollment and immediately before discharge (as well as before Session 1 for the TAP group), demographic and baseline data are collected from the individual with SCI and caregiver separately by a study coordinator. A study coordinator reads items aloud from an assessment packet (unless a participant explicitly requests a paper-and-pencil format) to the individual with SCI and caregiver, noting participants’ responses. The caregiver packet includes validated measures of caregivers’ quality of informal care provided, depression, relationship satisfaction, burden, caregiving self-efficacy, health status, and positive affect/well-being. The packet for the individual with SCI includes validated measures of functional status, perceptions of quality of informal care received, depression, relationship satisfaction, self-perceived burden, health status, and positive affect/well-being. In rare cases, after Data Collection 1 has been conducted, where the patient’s discharge is moved to a later date, data collection may be readministered to ensure data accuracy.

#### Data Collection 2-3

At 2 and 4 months, a study coordinator collects follow-up data from the individual with SCI and caregiver over the phone using the same validated measures as during the first data collection. A graphic depicting the study timeline can be seen in Figure 1.

**Figure 1 figure1:**
[figure not shown]
Randomized controlled trial timeline.

### Outcome Measures

#### Exemplary Care Scale

The Exemplary Care Scale is administered for both patient and caregiver and is an 11-item self-report questionnaire that assesses the extent to which caregivers engage or do not engage in activities that help care recipients maintain dignity and respect [24]. Parallel caregiver and care recipient versions are available with equivalent measurement properties.

#### Spinal Cord Independence Measure Version III

The Spinal Cord Independence Measure Version III is completed by the patient and is a 19-item self-report questionnaire that assesses functioning of individuals with SCI in 3 domains: self-care, respiration and sphincter management, and mobility. Higher scores indicate greater patient functioning [25].

#### Center for Epidemiologic Studies Depression Scale-Revised

The Center for Epidemiologic Studies Depression Scale-Revised (CESD-R) is completed for both the patient and caregiver. The 20-item CESD-R [26] is the revised version of the original CESD [27], and higher total scores reflect higher depression symptomology.

#### Self-Perceived Burden Scale

The Self-Perceived Burden Scale is completed by the patient and assesses care recipients’ feelings of dependence and guilt regarding their caregiver’s difficulties [28]. The Self-Perceived Burden Scale contains 10 items, and higher scores indicate higher self-perception of being a burden.

#### Zarit Burden Interview

The Zarit Burden Interview [29] is completed by the caregiver and is a 22-item, self-report measure of caregiver burden with items referring to the caregiver and patient relationship and evaluating the caregiver’s health condition, psychological well-being, finances, and social life. Higher total scores indicate greater burden.

#### Revised Scale for Caregiving Self-Efficacy

The Revised Scale for Caregiving Self-Efficacy [30] is completed by the caregiver and measures 3 domains of caregiving self-efficacy: obtaining respite, responding to disruptive patient behaviors, and controlling upsetting thoughts.

#### 12-Item Short Form

Both the patient and caregiver complete the 12-item Short Form (SF-12). The SF-12 is one of the most widely used assessments of HRQoL in individuals with neurological conditions and their caregivers [31]. The SF-12 has 8 dimensions: physical function, role-physical, bodily pain, general health, energy/vitality, social function, role-emotional, and mental health. Higher scores indicate better HRQoL.

#### SCI-QOL Positive Affect and Well-Being Short Form

The Positive Affect and Well-Being Short Form [32] is completed by both the patient and caregiver and is a 10-item version of the National Institutes of Health Patient-Reported Outcomes Measurement Information System that has been tailored and optimized for the SCI population. Higher scores reflect greater positive affect and well-being.

### Data Analysis

A Greenhouse-Geisser–adjusted RMANOVA with 1 fixed effect of treatment condition (TAP vs control), the repeated measures over time (baseline and 2 and 4 months after discharge), and the treatment condition by time interaction will be conducted for the set of dependent variables. If an omnibus effect is found, follow-up Holm-Bonferroni–corrected ANOVAs will identify specific locations of effects. Our research has shown that these dependent variables rarely correlate with each other higher than .60 in SCI caregivers [5] so do not reach the .70 level that is often identified as problematic in RMANOVA [33].

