### Participants, Recruitment, and Sample Size

The eligibility criteria for individuals with SCI and caregivers are the following: (1) between the ages of 18 and 89 years; (2) able to verbally communicate in English; (3) access to a computer, telephone, or other device capable of telecommunication; (4) no other serious mental or neurological disorders; (5) no active serious substance use disorder; and (6) being a dyad composed of 1 individual with a new diagnosis of SCI or significant new loss of function related to an old SCI and 1 individual identifying as a new informal caregiver. All individuals with SCI are those participating in a comprehensive residential rehabilitation program.

A power analysis was performed using G*Power 3.1. An estimated medium effect size of Cohen *f*=.25 was used to determine the sample size needed for a repeated-measures multivariate analysis of variance (RMANOVA) with 3 time points and 2 groups. With 80% power (1 - β), a sample size of 44 dyads is needed in order to detect the hypothesized medium-sized effects on the various outcomes. We selected a 48-month enrollment period because, based on SCI admissions data and previous studies conducted at the 2 rehabilitation sites, this window is necessary to enroll 44 patient-caregiver dyads (n=88), of which 22 dyads will be in the treatment group and 22 will be in the control group. This RMANOVA would uncover all large and medium-sized effects, but no small-sized effects.

Recruitment is conducted on site and in-person by either the research coordinator or the site’s principal investigator (PI). Patient-caregiver dyads are randomly assigned to the TAP treatment or control group, and each individual with SCI and caregiver is paid US $20 per data collection for a total of US $60 each.

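### The follow-up gate is any omnibus effect, so model terms that are poor tests of TAP, or no test of it, can open it; name one baseline-referenced treatment test as the only gate

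*Protocol article*

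**What the plan says.** The Data Analysis section plans an RMANOVA, adjusted by Greenhouse-Geisser. Its first two terms are given in these words: "with 1 fixed effect of treatment condition (TAP vs control), the repeated measures over time (baseline and 2 and 4 months after discharge". The same sentence of the article then adds a third term: "and the treatment condition by time interaction will be conducted for the set of dependent variables". The model thus has three terms: condition, time, and condition by time. The decision rule comes next: "If an omnibus effect is found, follow-up Holm-Bonferroni–corrected ANOVAs will identify specific locations of effects". The rule names no term, and Holm-Bonferroni is attached only to the follow-up ANOVAs.

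The Data Collection section fixes when baseline is taken: "After enrollment and immediately before discharge (as well as before Session 1 for the TAP group), demographic and baseline data are collected". Baseline therefore precedes any TAP session, yet it is one of the three levels of the repeated factor.

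The sample-size paragraph does not settle which term is meant. It says "An estimated medium effect size of Cohen *f*=.25 was used", names the design as a "repeated-measures multivariate analysis of variance (RMANOVA) with 3 time points and 2 groups", and arrives at 44 dyads, 22 per arm, at 80% power. It gives no alpha, no correlation between visits and no powered effect.

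**The concern.** Two of the three terms compare TAP with control, and the third does not compare the arms at all. A rule that proceeds on whichever omnibus effect appears has three weaknesses.

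- The condition main effect is a poor measure of TAP. One third of its average comes from a visit that TAP cannot influence, so a real benefit is diluted and a chance difference at baseline counts towards it.
- The two treatment terms use different parts of the data (each dyad's mean over visits, and the contrasts between visits). Accepting either gives two chances of a false signal at the omnibus stage.
- Change over time common to both arms would open the follow-up stage with no treatment signal. The omnibus test would then no longer protect the follow-up tests.

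The Discussion makes dissemination of the intervention conditional on significant results, so what counts as significant should be fixed before analysis.

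**Working it through.** **Inputs.** From the article: 22 dyads per arm, 3 visits, f = 0.25, 80% power, outcome correlations rarely above 0.60. The Outcome Measures section describes 12 scale-by-respondent scores, and the Data Collection section lists 7 constructs per person, hence 14. Assumed: alpha 0.05 per test, equal visit correlation ρ between 0.3 and 0.7, normal outcomes.

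**1. The plan's own figure.** With G*Power's repeated-measures formulas (N = 44, m = 3):
- Interaction: λ = f²·N·m·ε/(1−ρ). With ρ = 0.5 and ε = 0.5, λ = 0.0625 × 44 × 3 × 0.5/0.5 = 8.25 on 1 and 42 df; power 0.801.
- Condition main effect: λ = f²·N·m/(1+2ρ). With ρ = 0, λ = 8.25 on 1 and 42 df; power 0.801.

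The 44 dyads reproduce under both, so the figure does not show which term was intended. At ρ = 0.5 the two differ widely: the main effect would need 86 dyads, the interaction with ε = 1 only 28.

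**2. Dilution.** With an arm difference of 0 at baseline and d at both follow-ups, the main effect estimates (0 + d + d)/3 = 2d/3. For d = 0.5 SD and ρ = 0.5, the three-visit mean has variance (1+2ρ)/3 = 0.667. The standard error is √(2/22 × 0.667) = 0.246 and the ratio 0.333/0.246 = 1.35, so power is about 0.27 (normal approximation). A baseline-adjusted mean of the two follow-ups has variance (1+ρ)/2 − ρ² = 0.5. The standard error is 0.213 and the ratio 0.5/0.213 = 2.35, so power is about 0.65. At ρ = 0.3, 0.5 and 0.7 the main effect gives 0.33, 0.27 and 0.24, and the baseline-adjusted contrast 0.60, 0.65 and 0.79.

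**3. Main effect against interaction.** With t and F distributions and d = 0.5, the main effect has power 0.262 and the interaction 0.373 at ρ = 0.5. At ρ = 0.3 the order reverses: 0.315 and 0.276.

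**4. Chance baseline difference.** The standard error of a baseline difference is √(2/22) = 0.302 SD. A gap of 0.5 SD or more in either direction is 1.66 standard errors, about 10% of trials per outcome. Given a gap b and no treatment effect, the expected main effect is b(1+2ρ)/3, which is 0.33 SD for b = 0.5 and ρ = 0.5. Its conditional false-positive rate is about 12% by approximation and about 14-15% by simulation.

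**5. Error rates with no TAP effect.** If the two treatment tests are independent, 1 − 0.95² = 9.75%. The rows below are simulations at 22 per arm and ρ = 0.5, with Hotelling T² for the omnibus tests and Holm within each term for the follow-ups. Ranges cover different outcome correlations.

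| Event | 7 outcomes | 12 outcomes | 14 outcomes |
|---|---|---|---|
| At least one treatment omnibus test significant | 9.9-10.0% | 8.7-10.0% | 9.6% |
| Named outcome claimed, each term behind its own omnibus test | 3.2% | 1.7-2.6% | 1.6% |
| Named outcome claimed, any of the three terms opens the gate, 0.5 SD change common to both arms | 7.8-9.1% | 4.4-8.9% | not run |

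With no time change, the any-term gate gives about 2-4%. If one Holm family spanned both treatment terms, the rate stayed at or below about 4.5%, but the article does not define such a family. With the interaction as the only gate, the omnibus rate is 4.7-5.1%.

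**The case against.** A reader might infer that the trial's false-positive rate for TAP is about 10%, twice nominal. The document does not support that. The written procedure has two stages, and when each term stands behind its own omnibus test a false claim on a named outcome is well below 5%. The 10% is only the chance that at least one treatment omnibus test is significant, before any outcome is named.

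Nor does the article say that a condition main effect would be claimed as efficacy. It lists the usual terms of the model, it names the interaction explicitly, and its Study Design section calls the design before-and-after, which points to the interaction. This stands: the text allows the main effect to count but does not say it will.

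Naming the confirmatory term and alpha is often left to a full protocol or SAP. That excuses the missing alpha. It does not dispose of the point, because the article does state a decision rule, and that rule admits any term.

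Two further points stand. Randomisation keeps the main effect's unconditional error at its nominal level, so the figure in step 4 applies only to trials with that imbalance. A plain follow-up-minus-baseline contrast is also exposed to it: 12.7%, 10.6% and 8.6% at ρ = 0.3, 0.5 and 0.7, with 8.9%, 8.2% and 6.9% for the interaction. And the main effect is not always the weaker route, as step 3 shows.

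The defence from the two-stage structure has a limit, however. It assumes that the time effect does not open the gate. The Introduction describes the first months as particularly stressful for caregivers, so common change over time is plausible.

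**Conclusion.** The point holds as a defect in the decision rule, of moderate size. Any of three terms can start the follow-up tests: one tests TAP properly, one is diluted to two thirds and takes in chance baseline differences, and one does not test TAP. The dilution needs no assumption about alpha; it follows from the visit schedule for a benefit of equal size at both follow-ups.

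At an assumed 5% per test, the omnibus-stage false-positive rate for the two treatment terms is about 9-10%. The rate for a false claim on a named outcome is about 2-4% with each term behind its own omnibus test. It is about 4-9% if a common change, assumed at 0.5 SD, opens the gate and Holm is applied within each term. These figures rest on the assumed alpha, normal outcomes, visit correlation 0.5 and 7 to 14 outcomes. They do not show that the error of the final claim is doubled, or that the investigators intend to rely on the main effect.

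**What to change.** In the Data Analysis section, state that the condition-by-time interaction, or preferably one planned baseline-adjusted contrast between arms over the 2- and 4-month visits, is the only efficacy test and the only gate. Define the Holm family as those tests across all outcomes. State that the condition and time main effects are descriptive, trigger no follow-up tests and support no claim about TAP. The baseline-adjusted contrast is preferable because it uses baseline as a covariate, which deals with chance imbalance, and because it has the higher power in step 2.

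The cost is a sentence or two of wording, settled before the data are analysed, with no extra data. If the baseline-adjusted contrast is chosen, the model sentence must change as well, because that contrast is not a term of the stated RMANOVA. The downside is that the second route to a positive result is lost. That route can be more powerful than the interaction when visit correlation is low (about 0.3), but it was less powerful than the baseline-adjusted contrast at every correlation examined.

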### Setting

The TAP program is delivered via telehealth at a Veterans Affairs (VA) medical center and an academic medical center in the same urban area.

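### Modelling baseline as a third outcome visit makes the planned RMANOVA interaction test valid but inefficient; a baseline-adjusted mixed model would give more power from the same 44 dyads if the effect lasts

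*Protocol article*

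**What the plan says.** The Data Analysis section fixes an RMANOVA, adjusted by the Greenhouse-Geisser method and specified as one "with 1 fixed effect of treatment condition (TAP vs control), the repeated measures over time (baseline and 2 and 4 months after discharge"), together with the condition-by-time interaction, for the set of outcomes. An omnibus effect is followed by Holm-Bonferroni-corrected ANOVAs. Data Collection 1 takes place before discharge and, in the TAP arm, before Session 1. The two follow-ups are by telephone at 2 and 4 months.

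Under Participants, Recruitment, and Sample Size, the size comes from a G*Power calculation whose design is a "repeated-measures multivariate analysis of variance (RMANOVA) with 3 time points and 2 groups". On the assumed effect the section says: "An estimated medium effect size of Cohen *f*=.25 was used to determine the sample size needed". Its result reads: "With 80% power (1 - β), a sample size of 44 dyads is needed". The 48-month recruitment period is set because "this window is necessary to enroll 44 patient-caregiver dyads (n=88"). The split between arms is equal: "of which 22 dyads will be in the treatment group and 22 will be in the control group". The number needed and the number to be enrolled are the same.

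The article does not state the between-visit correlation, the alpha used for the power calculation, or how missed visits are handled.

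**The concern.** Baseline is measured before treatment in a randomised trial, so it cannot carry a treatment effect. Entering it as a response has two consequences.

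- The condition main effect averages in a visit with no effect. A sustained 0.5 SD difference becomes 0.5 × 2/3 = 0.33 SD.
- The treatment effect must therefore be sought in the interaction. With three visits this has 2 df and rests on change-type contrasts, which carry more noise than an analysis conditional on baseline.

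The trial has little room to recover that loss through numbers. The Results section reports 31 dyads enrolled by March 2021, with analysis due to begin in March 2022, and the target includes no allowance for loss. Classical RMANOVA needs a complete set of visits, so each missed call would take the analysis below 44 unless scores are imputed.

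**Working it through.** **Inputs from the article.** N = 44 dyads, 22 per arm; three visits (m = 3); f = .25; 80% power; baseline before Session 1.

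**Assumed, because not stated.** Two-sided alpha .05; equal correlation ρ between visits, varied over a range; unit SD; one outcome. The .60 quoted in Data Analysis is a correlation between outcomes, not between visits.

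**Step 1: the plan's own figure.** For the interaction, λ = N·m·f²·ε/(1−ρ) with 2ε and 2(N−2)ε df.

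- ρ = .5, ε = .5: λ = 44 × 3 × .0625 × .5/.5 = 8.25 on 1 and 42 df, power 80.1%. N = 44 is reproduced.
- ρ = .2, ε = 1: λ = 8.25/.8 = 10.31 on 2 and 84 df, power 81.3% (80% is reached at N = 43).
- ρ = .5, ε = 1: λ = 16.5, power 95.6% (N = 28 would do).
- Between-groups test with ρ = 0: λ = 8.25, power 80.1%. N = 44 again.

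So 44 is reproducible, but only under settings that the article does not give.

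**Step 2: sustained 0.5 SD effect at both follow-ups, complete data.**

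- Planned interaction: λ = (N/4)·d²·(2/3)/(1−ρ), F on 2 and 84 df (ε = 1 under this correlation pattern).
- Variance of the two-visit mean given baseline: v = (1+ρ)/2 − ρ².
- 2-df adjusted test: λ = (N/4)·d²/v, F on 2 and 40 df.
- 1-df adjusted average: noncentrality d/√(4v/N), t on 41 df.

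At ρ = .5:

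- interaction λ = 11 × .25 × .667/.5 = 3.67
- v = .75 − .25 = .50
- joint λ = 11 × .25/.50 = 5.5
- average noncentrality .5/√(2/44) = 2.345

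| ρ | v | Planned interaction | 2-df adjusted | 1-df adjusted average |
|---|---|---|---|---|
| .3 | .56 | 28% | 47% | 58% |
| .5 | .50 | 37% | 51% | 63% |
| .7 | .36 | 58% | 66% | 77% |
| .8 | .26 | 76% | 81% | 89% |

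Allowing for estimation of the baseline slope lowers the adjusted figures by about one point. The condition main effect at ρ = .5 has 26% power.

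**Step 3: where the gain comes from.** Size the sustained effect so that the planned interaction has 80% power.

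- A 1-df test of change from baseline has 87%. This part is due to the degrees of freedom alone.
- The 2-df adjusted test has 98, 92, 86 and 83% at ρ = .2, .5, .7 and .8. This part is due to baseline adjustment alone.
- The 1-df adjusted average, which combines both, has 99, 96, 93 and 90%.

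**Step 4: fading effect, 0.8 SD at 2 months and 0 at 4 months.** At ρ = .5:

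- Planned: λ = 11 × .64 × .667/.5 = 9.39, power 77%.
- 2-df adjusted: λ = 11 × .64 × 1.5 = 10.56, power 81%.
- 1-df average: .4/√(2/44) = 1.876, power 45%.

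At ρ = .7 the three are 95%, 95% and 58%.

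**Step 5: missed visits (illustration only).** This is a simulation with 1500 trials per setting, a 0.7 SD sustained effect and an assumed 20% random dropout. It compares the interaction test on complete cases with a baseline-adjusted mixed model on available data.

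| ρ | Interaction, no dropout → 20% | Mixed model, no dropout → 20% |
|---|---|---|
| .5 | 62% → 52% | 87% → 83% |
| .7 | 86% → 79% | 96% → 93% |

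Most of the gap is there before any dropout. Null rejection rates across the settings simulated were 4.1 to 5.3% for the interaction and 4.4 to 6.2% for the mixed model, whose df were approximate.

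**The case against.** The strongest reply is that this is a question of efficiency, not of error. The planned interaction holds its Type I error under randomisation. That stands, and it limits how serious the point is.

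A reader might infer that the plan wastes baseline. It does not: the interaction uses baseline through change contrasts. The variance of the change contrast relative to the adjusted one is 1.5(1−ρ)/v, which falls from 2.14 at ρ = .2 to 1.15 at ρ = .8.

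A reader might also infer that the plan drops every incomplete dyad and so biases the comparison. The article does not say this. Complete-case analysis is the default of the named method, and rules for imputation may sit in an analysis plan that is not shown.

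The 0.5 SD benchmark is mine. If f = .25 is read as an interaction effect in the convention of Step 1, a sustained difference d gives f = d/√18, so d = 1.06 SD. At that size the planned test has 81% power at ρ = .2 and 96% at ρ = .5, against over 99% for the adjusted average in both cases. The table therefore does not show that the plan's stated 80% is wrong.

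The two-visit average is not always better. Sessions end 6 weeks after discharge, so a fading effect is plausible, and Step 4 shows a real loss. This objection does not defeat the 2-df adjusted test. With benefit at 2 months only, sized for 80% planned power, that test has 82, 80 and 79% at ρ = .5, .7 and .8.

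The calculations cover one outcome, whereas the plan has an omnibus test over several. Separate models with no correction would weaken the plan, so multiplicity control has to stay.

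Site is a minor matter. The trial runs at "a Veterans Affairs (VA) medical center and an academic medical center in the same urban area", and the Randomization section describes no stratification by site, so leaving site out of the model does not invalidate the test.

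**Conclusion.** The point holds as one of efficiency. The article fixes a valid analysis that gives away power at a sample size with no reserve.

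For a sustained 0.5 SD effect, like-for-like baseline adjustment adds about 19 points at ρ = .3 (28 to 47%), 14 at .5, 8 at .7 and 5 at .8. Moving to a 1-df average as well brings the total gain to 30, 26, 19 and 13 points.

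These sizes rest on 22 complete dyads per arm, equal between-visit correlations, a single uncorrected outcome, alpha .05 and an effect that lasts. For an effect confined to 2 months, the 2-df adjusted test roughly matches the planned one and the average does clearly worse. The effect of missed visits depends on handling rules that are not shown, and the conclusion does not need it.

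**What to change.** Before analysis starts, replace the RMANOVA for each outcome with a linear mixed model.

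- **Data:** all available 2- and 4-month scores from randomised dyads.
- **Fixed effects:** treatment, visit, treatment-by-visit and the baseline score; site is optional.
- **Covariance:** unstructured within person.
- **Efficacy test, chosen in advance:** either the joint 2-df treatment effect over both visits, which is robust to fading, or the 1-df average of the two visits. If the average is chosen, state that it loses power when benefit exists only at 2 months.
- **Multiplicity:** apply the Holm-Bonferroni correction across outcomes to that test.
- **Missed visits:** state how they are handled.
- **Sensitivity analysis:** the planned RMANOVA.

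The cost is a change of wording in the analysis plan and one model degree of freedom for baseline, plus one more if site is included. No new data are needed.
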